## Abstract

**Background:**

Depressive symptoms are common in gastroenterology practice but often missed due to patient stigma and the limitations of self-report questionnaires. This detection gap limits patient access to necessary mental health care. Although vascular dysfunction has been associated with depressive symptoms, the role of accessible peripheral vascular and autonomic measures in relation to concurrent questionnaire-defined depressive symptom burden in gastroenterology settings remains insufficiently studied. This study aims to evaluate whether vascular and autonomic measures are associated with screening-positive depressive symptom burden in chronic atrophic gastritis and whether they may provide adjunctive information beyond conventional clinical and histological variables.

**Methods and analysis:**

This multicenter observational protocol plans to enroll 450–520 adults aged 20–60 years with histologically confirmed chronic atrophic gastritis from four centers in China. The study includes dorsalis pedis artery Doppler ultrasonography, brachial–ankle pulse wave velocity assessment, gastrointestinal and histological evaluation, and standardized psychological questionnaires. The primary analysis examines whether vascular and autonomic measures are associated with concurrent screening-positive depressive symptom burden (PHQ-9 ≥ 10) and whether they provide incremental information beyond clinical and histological variables. Multivariable regression and internally validated discrimination analyses are used. No participants have been enrolled and no data have been collected at the time of submission.

**Discussion:**

The findings may help inform future validation studies and multidisciplinary assessment strategies in gastroenterology settings.

**Conclusion:**

This study aims to evaluate whether vascular and autonomic measures are associated with screening-positive depressive symptom burden in chronic atrophic gastritis and whether they may provide adjunctive information beyond conventional clinical and histological variables.

**Clinical trial registration:**

[ClinicalTrials.gov], identifier [NCT07319338].

## Introduction

1

Chronic gastritis and related upper gastrointestinal disorders are common in clinical practice and often coexist with psychological symptoms such as depression and anxiety (1, 2), within a broader gut-brain framework that has attracted increasing attention (3–5). Within this broader group, chronic atrophic gastritis (CAG) is a chronic inflammatory gastric disorder characterized by glandular loss, with or without intestinal metaplasia, and is recognized as a premalignant condition in the Correa cascade. CAG is most commonly associated with Helicobacter pylori infection or autoimmune mechanisms and often requires long-term surveillance because of its pathological progression and cancer risk. We selected CAG as the target population because it provides a clinically and histologically defined gastroenterology setting in which persistent gastrointestinal burden, pathological severity, and psychological distress may coexist.

Even when psychological distress is clinically relevant, depressive symptoms may still be under-recognized in routine gastroenterology care. Patients who present mainly with somatic complaints may be less likely to describe emotional symptoms spontaneously, and self-report instruments alone may not fully capture distress in this setting. For this reason, it may be useful to explore adjunctive, non-psychiatric assessment approaches that can help clinicians open conversations about mental health in a way that feels more acceptable to patients.

Growing evidence suggests that vascular dysfunction and arterial stiffness are associated with depressive symptoms (6–8). In the present study, vascular and autonomic measures are not intended to explain the pathogenesis of CAG itself. Rather, they are being examined as accessible physiological measures that may be associated with concurrent depressive symptom burden within a clinically defined gastroenterology population. Brachial–ankle pulse wave velocity (baPWV) (9–11) and ankle–brachial index (ABI) (12) are established markers of vascular status, while Doppler ultrasound offers a practical way to assess peripheral hemodynamics in routine clinical settings (13). In this framework, gastrointestinal pathology provides the disease context, whereas dorsalis pedis artery Doppler indices, baPWV, and heart rate variability are evaluated as potential adjuncts to symptom-based assessment (14, 15). Dorsalis pedis ultrasound was selected primarily for pragmatic reasons, including superficial accessibility, feasibility in routine outpatient settings, and compatibility with standardized repeated measurement, rather than because of established biological specificity for depressive symptom burden. In the present protocol, it is therefore treated as an accessible peripheral hemodynamic marker within a multimodal assessment framework rather than as a uniquely informative vascular bed.

Currently, most studies in this area remain focused on symptom questionnaires (16), inflammatory or microbial markers (17, 18), or broader gut–brain frameworks without a specific emphasis on identifying depressive symptom burden in routine gastroenterology settings (19, 20). This leaves a practical gap in adjunctive assessment approaches that may be acceptable to patients who primarily seek help for somatic gastrointestinal complaints. In this context, vascular and autonomic measures may offer an additional source of clinically interpretable information that can complement, rather than replace, conventional psychological assessment.

Our interest in this question was also informed by preliminary observations from our earlier work in related gastroenterology populations, although those findings are not yet published and therefore are not presented here as formal supporting evidence.

Against this background, we designed a multicenter observational study in routine gastroenterology settings. The primary aims are to characterize multimodal phenotypes across PHQ-9-defined depressive symptom strata, examine cross-sectional associations between vascular/autonomic markers and concurrent depressive symptom burden, and assess whether these markers provide incremental information beyond clinical and histological variables. This protocol is intended as a phenotyping and association study rather than a mechanistic validation study.

## Study objectives

2

(1)Characterize multimodal phenotypes across depressive symptom strata.(2)Quantify independent associations between distal vascular markers and questionnaire-defined depressive and anxiety symptom burden with prespecified adjustment.(3)Develop and internally validate a parsimonious multivariable model for identifying PHQ-9 screening-positive depressive symptom burden, and evaluate the incremental information provided by vascular and HRV markers beyond clinical and histological variables.(4)Descriptively summarize selected workflow-related indicators, including assessment completion, time burden, and referral uptake, to inform future practice-oriented and validation-focused research.

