##### Anxiety

3.3.4.2

The Generalized Anxiety Disorder-7 (GAD-7) assesses anxiety symptoms (total score: 0–21).

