#### Secondary outcomes

3.4.2

① PHQ-9 total score as a continuous variable (gradient of depression severity);

② GAD-7 total score (anxiety severity);

③ PSQI total and subscale scores (subjective sleep quality);

④ Descriptive workflow indicators: To characterize selected practical aspects of the assessment process in routine gastroenterology settings, we summarize:

Screening completion rate: The proportion of eligible patients who consent to and complete the vascular and psychological assessment.

Referral uptake: The proportion of screen-positive patients (PHQ-9 ≥ 10) who complete a mental health consultation within 4 weeks, as verified by medical records.

Time burden: The median time added to the routine gastroenterology workflow per patient.

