#### Group comparisons

3.5.2

Participants will be grouped according to the primary outcome definition (PHQ-9 ≥ 10 vs. < 10). Between-group comparisons will evaluate differences in study indicators [gastric histopathology, vascular indices (e.g., RI, PI), baPWV, ABI/TBI, HRV, and scale scores] between PHQ-9 screening groups (≥0 vs. <10), while baseline demographics/clinical characteristics will be presented descriptively (Table 1). Comparisons of multimodal vascular, autonomic, and psychiatric measures between PHQ-9 screening groups (≥10 vs. <10) will be presented in Table 2.

**TABLE 1 T1:** Baseline characteristics of the study participants according to depressive symptom status.

Variable	Total (*n* = …)	PHQ-9 < 10 (*n* = …)	PHQ-9 ≥ 10 (*n* = …)	SMDs
Demographics				
Age, years				
Female, *n* (%)				
Body mass index, kg/m^2^				
Lifestyle and comorbidities				
Current smoker, *n* (%)				
Alcohol use, *n* (%)				
Hypertension, *n* (%)				
Diabetes mellitus, *n* (%)				
Dyslipidaemia, *n* (%)				
History of cardiovascular disease, *n* (%)				
Gastric/endoscopic–histological features				
OLGA stage 0–II, *n* (%)				
OLGA stage III–IV, *n* (%)				
OLGIM stage 0–II, *n* (%)				
OLGIM stage III–IV, *n* (%)				
*H. pylori* positive, *n* (%)				
Psychiatric and symptom scales				
GAD-7 total score				
PSQI total score				
GSRS total score (and subscales if used)				
HRQoL physical component score				
HRQoL mental component score				

**TABLE 2 T2:** Multimodal vascular, autonomic and psychiatric profiles according to depressive symptom status.

Variable	PHQ-9 < 10 (*n* = …)	PHQ-9 ≥ 10 (*n* = …)
Peripheral vascular ultrasound (dorsalis pedis artery)		
Inner diameter (mm)		
PSV (cm/s)		
EDV (cm/s)		
RI		
PI		
Triphasic waveform, *n* (%)		
Biphasic waveform, *n* (%)		
Monophasic waveform, *n* (%)		
Arterial stiffness and peripheral artery indices		
baPWV (cm/s)		
ABI		
TBI (if available)		
Autonomic and physiological measures		
Systolic blood pressure (mmHg)		
Diastolic blood pressure (mmHg)		
Resting heart rate (bpm)		
SDNN (ms)		
*RMSSD (ms)*		
Psychiatric and symptom measures		
GAD-7 total score		
PSQI total score		
GSRS total score (and subscales if used)		
HRQoL physical component score		
HRQoL mental component score		

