Baseline characteristics are summarized descriptively and quantified using standardized mean differences (SMDs) rather than hypothesis testing; *p*-values will not be reported for Table 1. Formal statistical testing is used for prespecified exposure–outcome comparisons and model estimation as described below:

① *t*-test for normally distributed continuous variables with equal variances;

② Mann–Whitney U for non-normal or heteroscedastic variables;

③ χ^2^ test or Fisher’s exact test for categorical data.

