#### Multivariable models

3.5.3

Logistic regression will assess the independent association between key vascular markers (e.g., dorsalis pedis RI, PI, waveform classification, baPWV, ABI/TBI) and PHQ-9 ≥ 10, adjusting for study center (as a fixed effect), age, sex, body mass index, smoking status, alcohol use, education level, marital status, hypertension, diabetes, dyslipidemia, relevant medication use, and histopathological severity (e.g., OLGA/OLGIM stage or Updated Sydney graded atrophy/intestinal metaplasia). Results will be reported as odds ratios (OR) with 95% confidence intervals (CI). We will restrict the number of predictors in the primary multivariable models to approximately 10–12, prioritizing predefined key vascular indices and major confounders, with additional variables explored only in sensitivity analyses.

In a secondary analysis, linear regression will evaluate the association between vascular indices and PHQ-9 as a continuous outcome. Prior to model fitting, collinearity among vascular indices (e.g., RI, PI, baPWV, ABI/TBI) will be assessed (e.g., via variance inflation factors); if substantial collinearity is detected, we will reduce the number of simultaneously entered vascular predictors or construct composite scores to improve model stability. Model assumptions will be checked; transformations or generalized linear models will be applied as needed. Continuous predictors will be modeled linearly in the primary analysis unless clear evidence of non-linearity is identified; if linearity assumptions appear violated, appropriate transformations or restricted spline terms will be explored in secondary analyses. The results of the prespecified logistic and linear regression analyses will be presented in Table 3.

**TABLE 3 T3:** Multivariable associations between vascular measures and depressive symptoms.

Table 3A | Logistic regression (outcome: PHQ-9 ≥ 10).			
Predictor	Model	OR (95% CI)	*P*-value
Dorsalis pedis RI (per 0.1 increase)	Model 1 (basic)		
Dorsalis pedis RI (per 0.1 increase)	Model 2 (extended)		
Dorsalis pedis PI (per 0.1 increase)	Model 1 (basic)		
Dorsalis pedis PI (per 0.1 increase)	Model 2 (extended)		
Monophasic vs. triphasic waveform	Model 2 (extended)		
baPWV (per 100 cm/s increase)	Model 2 (extended)		
ABI (per 0.1 increase)	Model 2 (extended)		
SDNN (per 10 ms increase)	Model 3 (with HRV)		
RMSSD (per 10 ms increase)	Model 3 (with HRV)		
Age (per 10-year increase)	All models (adjusted)		

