### Prespecified multivariable association analyses

4.3

Prespecified multivariable analyses will examine the associations between vascular and autonomic measures and depressive symptom burden. The primary model will use PHQ-9 ≥ 10 as the binary outcome in logistic regression. Secondary analyses may additionally examine PHQ-9 total score as a continuous outcome. Effect estimates will be reported with corresponding confidence intervals, with interpretation focused on effect size, precision, and consistency rather than on isolated statistical significance.

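### Objective 2 promises adjusted vascular associations with anxiety as well as depression, but every planned regression has a PHQ-9 outcome, so the anxiety half gets no estimate (minor)

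*Protocol article*

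**What the plan says.** Section 2, Objective 2, sets this task: "Quantify independent associations between distal vascular markers and questionnaire-defined depressive and anxiety symptom burden with prespecified adjustment". It fixes the exposures (distal vascular markers), two outcomes (depressive and anxiety burden) and the kind of estimate (independent, with adjustment decided in advance).

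The anxiety instrument is defined in section 3.3.4.2: "The Generalized Anxiety Disorder-7 (GAD-7) assesses anxiety symptoms (total score: 0–21". Its total appears in the secondary outcome list of section 3.4.2 as "GAD-7 total score (anxiety severity".

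Section 3.5.2 brings the scale scores into group comparisons. It says "Between-group comparisons will evaluate differences in study indicators", with PHQ-9 screening status as the grouping, and then "Comparisons of multimodal vascular, autonomic, and psychiatric measures between PHQ-9 screening groups (≥10 vs. <10) will be presented in Table 2". The tests are two-sample ones, for example "Mann–Whitney U for non-normal or heteroscedastic variables".

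In section 3.5.3 the logistic model has PHQ-9 at or above 10 as its outcome. The secondary model is described thus: "linear regression will evaluate the association between vascular indices and PHQ-9 as a continuous outcome". Section 4.3 says that the prespecified multivariable analyses will "examine the associations between vascular and autonomic measures and depressive symptom burden".

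**The concern.** An objective that promises an adjusted association needs a model with that outcome on the left-hand side. For depressive symptoms the article supplies several. For anxiety it supplies none, although the objective puts the two on the same footing and says that the adjustment is prespecified.

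Two things are at stake. First, a team that follows the article as printed will finish the study with part of Objective 2 unanswered. Second, if a GAD-7 model is added once data are in hand, its exposures and covariates will have been chosen late, and it could not be called prespecified in the sense that the objective claims.

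**Working it through.** No arithmetic applies. The check is to list every planned analysis, note its dependent variable, and then list every place where anxiety or GAD-7 occurs.

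**Planned models and their outcomes**

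| Place in the protocol article | Analysis | Dependent variable |
|---|---|---|
| 3.5.3, Table 3A | Logistic regression, Models 1–3 | PHQ-9 ≥ 10 |
| 3.5.3, Table 3B | Linear regression, Models A–C of that table | PHQ-9 total |
| 3.5.4 | Hierarchical Models A–C, compared by AUC | PHQ-9 ≥ 10 |
| 3.5.4 | Primary inferential model | PHQ-9 ≥ 10 |
| 3.5.4 | Secondary or exploratory list | Linear models named for PHQ-9 total only |
| 3.7 | Bootstrap internal validation | PHQ-9 ≥ 10 |
| 4.3 | Planned presentation of associations | PHQ-9 ≥ 10, with PHQ-9 total as secondary |
| 4.4 | Internal evaluation of models | PHQ-9 screening-positive status |

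The list in 3.5.4 also mentions penalized regression and composite scores without naming an outcome. Elsewhere both are tied to the models above: composite scores in 3.5.3 are a remedy for collinear vascular predictors, and penalization in 3.6 is a remedy for too few PHQ-9 events. Neither introduces an anxiety outcome.

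Number of planned models with GAD-7 or anxiety as the dependent variable: 0.

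**Where anxiety or GAD-7 does occur**

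1. Objective 2, as an outcome of the adjusted association.
2. Section 3.3.4.2, as an instrument.
3. Section 3.4.2, as a listed secondary outcome. This entry mentions neither vascular markers nor adjustment; those come from Objective 2.
4. Table 1, as a descriptive row with a standardized mean difference and no p-value.
5. Section 3.5.2 and Table 2, as a scale score compared between PHQ-9 groups by unadjusted tests.

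**Comparison with the objective.** Items 4 and 5 are the only planned uses of the GAD-7 data. They show how anxiety scores differ between patients above and below the PHQ-9 cut-off. They contain no vascular marker and no covariate, so they cannot supply what Objective 2 asks for. They fit Objective 1, which concerns phenotypes across depressive strata.

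**Could a GAD-7 model be read into the text?** Section 3.5.3 sends the results of the prespecified logistic and linear regressions to Table 3. Both panels of that table carry a PHQ-9 outcome in their title, which leaves no place for a GAD-7 model.

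**The case against.** The strongest reply is that this is an omission in a condensed article. Models for a single secondary outcome are often left to the full protocol or the analysis plan, neither of which is shown, and no sentence rules out an adjusted GAD-7 model. That would settle the matter if the article were silent on regression outcomes. It is not: it names each dependent variable, prints result tables titled by outcome, and sorts its further analyses into secondary and exploratory. Against that level of detail, a numbered objective with no matching model is a mismatch within the document.

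The reply does stand on severity. The aims in the Introduction, the framework in 3.1, the primary outcome, the primary model and the core hypothesis in 5.1 all concern depressive symptoms.

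Three stronger readings are tempting, and the document does not support them.

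- A reader might infer that the PHQ-9 group comparison is a rival, wrong analysis of the anxiety objective. The article never presents it as the analysis for Objective 2. A scale can describe strata under one objective and be an outcome under another.
- A reader might extend the point to sleep quality, because the PSQI is also a listed secondary outcome without a regression. No objective promises an adjusted PSQI association, so there is nothing for the analysis to contradict.
- A reader might argue that the gap hides whether any association is particular to depression. The protocol does not set that aim, and a separate GAD-7 model would not test it, since it would neither adjust for PHQ-9 nor compare the two associations.

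**Conclusion.** The point holds in a limited form. Objective 2 promises adjusted vascular associations for anxiety, and none of the models that the article specifies would estimate one. The objective and the analysis section need to be brought into line.

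This is a minor issue. No primary estimate, sample size or primary conclusion changes, and the study calls itself exploratory. The finding needs no numerical assumption. It rests on reading the regressions and table shells as the article's full statement of which outcomes are modelled. If an unseen analysis plan already holds a GAD-7 model, what remains is to make the article's section 3.5.3, Table 3 and section 4.3 agree with it.

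**What to change.** Choose one of two changes. The article states that no participant had been enrolled at submission, so either could be made before data collection.

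1. **Add the model.** In 3.5.3 and Table 3B, add a linear regression with the GAD-7 total as dependent variable. Use the same prespecified vascular exposures and the same adjustment set as the PHQ-9 linear model, label it secondary, and extend the sentence in 4.3 to match. The cost is one more regression on data already planned for collection and a few table rows. The small downside is a further set of secondary estimates, which must be read as such.
2. **Narrow the objective.** Remove anxiety from Objective 2 and label GAD-7 as descriptive in 3.4.2. This costs a wording change only, and gives up the adjusted anxiety estimate.

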## Methods

3

### Study design and setting

3.1

This is a multicenter observational study conducted in routine gastroenterology outpatient settings. The primary analytic framework is cross-sectional and focuses on concurrent depressive symptom burden at baseline. The study is designed to characterize multimodal phenotypes, examine associations between vascular markers and depressive symptoms, and develop an internally validated multivariable model for identifying PHQ-9 screening-positive depressive symptom burden within a histologically defined CAG population. The protocol is coordinated by the China Academy of Chinese Medical Sciences (lead center). At the time of submission, site activation has been completed for the China Academy of Chinese Medical Sciences and Hengshui Hospital of Traditional Chinese Medicine. Additional participating sites, including Beijing Anzhen Hospital and Liyang Hospital of Traditional Chinese Medicine, will begin recruitment only after completion of site-specific ethical approval and local activation procedures. The study design also allows for the potential inclusion of additional qualified centers during the recruitment phase to further enhance generalizability. Eligible adults with CAG are consecutively enrolled from gastroenterology outpatient clinics. We do not recruit from inpatient wards to maintain comparability with routine clinic screening workflows. All research procedures are conducted in accordance with a pre-established study protocol, which includes participant screening, informed consent acquisition, multimodal assessments, and data entry.

Author affiliations reflect institutional appointments and do not necessarily indicate site activation or participant recruitment responsibilities within the present protocol.

### Participants

3.2

Eligible participants will be patients diagnosed with chronic atrophic gastritis (CAG) confirmed by histopathology following upper gastrointestinal endoscopy at one of the participating hospitals. All subjects will be screened and registered according to standardized criteria.

